### Co-interventions

Data on the usage of co-interventions will be collected at every follow-up visit through an interview. Patients will be encouraged not to start any new conservative treatments they were not receiving at baseline. Besides no new pharmacological treatment, this also includes no new corticosteroid injections, physiotherapy, or the usage of a brace. They can, however, increase or decrease any pharmacological treatment they were receiving based on their complaints, continue an already ongoing physiotherapy treatment, or keep wearing a brace if they were using one. This information will be recorded.

### Outcome measurements

Outcome measurements will be recorded at baseline and 1, 4, 8, and 12 months after the procedure. The primary outcome is change of the knee injury and osteoarthritis outcome score (KOOS [14]) pain subscale score between baseline and 4 months follow-up. Secondary outcomes are the change of pain subscale score between baseline and 1, 8, and 12 months. Other secondary outcomes are the change of the remaining dimensions of the KOOS (symptoms, daily living, sport and recreation and quality of life), additional questionnaires, and the pressure pain threshold after 1, 4, 8, and 12 months.

Changes on MRI will be compared between baseline and after 1 and 4 months. All clinical trial study activities are summarized in Table 1.

**Table 1 Tab1:** Clinical trial study activities overview

	Study period						
	Enrolment/baseline	Intervention	Post-allocation				Close-out
Timepoint**	***− 2 weeks***	0	***Post-intervention***	***1 month***	***4 months***	***8 months***	***12 months***
**Enrolment:**							
**Eligibility screen**	**X**						
**Informed consent**	**X**						
**Randomization**	**X**						
**Allocation**	**X**						
**Interventions:**							
**Genicular artery embolization**		**X**					
**Sham procedure**		**X**					
**Assessments:**							
**Blood examination**	**X**						
**Usage of co-interventions**	**X**			**X**	**X**	**X**	**X**
**VAS pain**	**X**			**X**	**X**	**X**	**X**
**KOOS questionnaire**	**X**			**X**	**X**	**X**	**X**
**ICOAP questionnaire**	**X**			**X**	**X**	**X**	**X**
**painDETECT questionnaire**	**X**			**X**	**X**	**X**	**X**
**EQ-5D-5L questionnaire**	**X**			**X**	**X**	**X**	**X**
**Global perceived effect questionnaire**							**X**
**PPT measurement**	**X**			**X**	**X**	**X**	**X**
**MRI examination**	**X**			**X**	**X**		
**Adverse event assessment**			**X**	**X**	**X**	**X**	**X**
**Concealment of allocation assessment**			**X**				

#### Questionnaires

For the main outcome, the KOOS questionnaire is used [14]. This questionnaire consists of 42 questions divided into 5 subscales: pain (primary outcome), other symptoms, function in daily living (ADL), function in sport and recreation, and knee-related quality of life (QOL). Other questionnaires used are the Intermittent and constant osteoarthritis pain (ICOAP) [15], painDETECT [16], EuroQol 5 dimensions 5 levels (EQ-5D-5L) quality of life questionnaire [17], and a VAS (0–100 mm) score for pain, stiffness, and swelling. At the 12-month follow-up point, patients will be asked about the perceived effect of the treatment using the global perceived effect questionnaire [18]. All patients will fill in the questionnaires autonomously, but if some questions are not understood, they can ask the clinical researcher for assistance.

#### Pressure pain threshold testing

At baseline and each follow-up visit, pressure pain threshold testing (PPT) will be performed using an algometer with a tip of 1cm^2^ (Biometrics, MicroFET 2, Almere, The Netherlands). Measurements will be performed with the patient’s knee in 30° of flexion. The sites of measurements are at the medial and lateral joint space 2 cm medial and lateral to the inferior edge of patella, 2 cm above the superior border of the patella, and a peripheral site at the center of the brachioradialis muscle at the contralateral side from the treated knee. Pressure of gradually increasing intensity (10 N·s^−1^) is applied. The patient is instructed to say “stop” at the moment the sensation switches from pressure to painful. These measurements are repeated three times and are averaged to determine the pressure pain threshold. The sites are marked such that repeat measurements will be at the same location. Before measurements start, a test measurement will be done at a site not used for actual measurements for patients to get familiar with the measurements. Measurements are repeated 3 times and the average will be considered the pressure pain threshold. This method to determine the PPT has a high reliability with intra class correlation coefficients of 0.95–0.97 [19]. A cutoff limit of 120 N/cm^2^ was implemented to prevent tissue damage.

#### MRI examination

All patients will undergo MRI at baseline and at 1 and 4 months after treatment. Images will be acquired using a 3.0-T MR system with 70 cm bore (Signa Premier, GE, Chicago, IL, USA) equipped with an 18-channel dedicated knee coil (GE, Chicago, IL, USA). The MRI protocol consists of Double Echo Steady State (DESS), 3D PD (proton density) weighted fast spin echo, axial and sagittal T2 fat saturated (FS), sagittal MAGnetic resonance Image Compilation (MAGiC) synthetic imaging, dynamic contrast enhanced (DCE) MRI using DIfferential Subsampling with Cartesian Ordering (DISCO), and post contrast T1 weSPGR pulse sequences. During the DCE-MRI, 0.1 ml/kg gadovist (Bayer, Leverkusen, Germany) followed by 15 ml of saline will be administered at an injection speed of 1.0 ml/s using a contrast injector (GE, Chicago, IL, USA). This protocol was designed to assess the knee tissues semi quantitatively using the MRI Osteoarthritis Knee Score index (MOAKS [20]) and quantitatively using DCE-MRI and post contrast T1 acquisitions as well as T2-mapping of the articular cartilage using the MAGiC acquisitions.

### Adverse events and the data safety monitoring board

Adverse events (AE) are defined as any undesirable experience occurring to a subject during the study period, whether or not considered related to the intervention. One day after the procedure, the patients will be contacted and actively screened for the occurrence of any adverse events. Patients will be asked to report any changes in their health status. At every follow-up visit, patients will be actively screened for the occurrence of any AE.

Possible adverse events related to GAE are as follows: transient discoloration in the region of embolization due to non-target embolization or nerve damage due to non-target embolization. Only patients in the intervention group are subjected to these risks. All patients will receive local anesthesia and a small incision in the groin and are therefore subject to the risk of access-site hematoma and access-site infection. All patients undergo MRI with contrast agent injection and are therefore at risk for an allergic reaction to gadolinium.

After including 10 patients, a data and safety monitoring board (DSMB) will perform a safety analysis. The DSMB consists of an interventional radiologist, an orthopedic surgeon, and a biostatistician. The aim of this committee is to protect the interests of patients enrolled in this study and to evaluate the safety of the investigational intervention used in this trial. (S)AE’s and pain scores will be used to test if the intervention is deemed safe enough to continue the trial. The local ethical board will receive a report and will decide if the trial can continue. The members of this DSMB are independent of the trial. They were not involved in the creation of the protocol or have any competing interest.

Additionally, the trial conduct will be audited every 6 months by an independent auditor from the Department of Radiology & Nuclear Medicine of Erasmus MC.

### Sample size calculation

Calculations are partly based on the previous observational studies by Okuno et al. [6, 7]. Despite a possible placebo effect, which account for effect sizes up to 0.5 [21], they found effect sizes of > 5. For our study, we assumed we would require to demonstrate a large effect size of > 0.8 (strong effect) compared to sham embolization since GAE still is (minimally) invasive. Assuming this projected effect size of 0.8, and a standard deviation of 16 for the KOOS (100-0) pain score (estimated from multiple OA studies at Erasmus MC), beta of 0.80, and alpha of 0.05, 48 patients (*n* = 24 per study arm) are required to detect an increase (higher scores indicate less pain) in primary outcome measure of 8 points in the control group (placebo effect) compared to 21 points in the intervention group. The targeted sample size will be 58 to account for approximately 20% of patients lost to follow-up. We also expect a more homogeneous study population since all included subjects have an NRS pain score ≥ 4 and ≤ 8. With this sample size, and in case of lower variation in pain scores than SD of 16, we expect we could also detect smaller effect sizes between 0.5 (moderate effect) and 0.8.

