### Randomization, allocation concealment, and blinding

Patients will be randomized 1:1 using a random block size strategy with block sizes of 4 and 6. Randomization is performed using an online randomization tool (ALEA clinical: https://www.aleaclinical.eu/). The clinical researcher, blinded for randomization, will conduct the MRI scans, evaluate patients during follow-up, and will enter the patient data into an online database. The interventional radiologist who will perform the procedure will be automatically informed about the randomization result by email. The allocation will only be sent to the interventional radiologist and a third party within the department who safeguards the randomization code. All others, including the clinical researcher, treating orthopedic surgeon, and patients, will be blinded tot group allocation.

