### Statistical analysis

The primary outcome is the difference in KOOS pain subscale change from baseline to 4 months between both groups. Repeated measurements regression analysis for continuous variables will be performed, based on intention to treat analysis to determine a difference between groups. Generalized estimating equations (GEE) will be used to enable inclusion of all available measurements in the regression models even if they are correlated. It also allows us to adjust for unequal distribution of prognostic variables over the two groups, which easily can occur in smaller randomized clinical trials. Radiographic severity, pain pressure threshold, and degree of sensitized pain according to painDetect will all be tested for equal distribution and, if more than 10% different, we will test if this variable changes the estimate with more than 10%. If this is the case, the variable will be included in the adjusted analysis. The adjusted analysis will be the primary analysis, but we will also present the unadjusted analysis. If some of the patients do not receive the treatment as allocated, we will also perform a per protocol analysis where the patients that did not comply with the allocated treatment will be excluded. Repeated measurement regression analysis will also be used for all continuous secondary outcomes: KOOS subscales, VAS, ICOAP, painDETECT, EQ-5D-5L, and PPT scores.

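### The sample-size statement has small errors: power is labelled beta, and 58 patients cover about 17% loss rather than 20%, so nominal power after 20% loss is slightly under 80%

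*Protocol article*

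**What the plan says.** All of the planning figures are in the Sample size calculation section of the Protocol article.

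- Effect size: "Assuming this projected effect size of 0.8".
- Spread: "a standard deviation of 16 for the KOOS (100-0) pain score".
- Expected improvements: "8 points in the control group (placebo effect) compared to 21 points in the intervention group", a difference of 13 points.
- Error rates and result: "beta of 0.80, and alpha of 0.05, 48 patients", that is, 24 per arm.
- Allowance for loss: "The targeted sample size will be 58 to account for approximately 20% of patients lost to follow-up".

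The section states neither whether alpha is two-sided nor which test or formula was used. Allocation is 1:1 (Randomization, allocation concealment, and blinding). The Statistical analysis section plans a repeated-measures model: "Generalized estimating equations (GEE) will be used to enable inclusion of all available measurements in the regression models".

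**The concern.** Three things in one paragraph do not fit together.

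1. Beta is the type II error rate. Read literally, a beta of 0.80 means 20% power.
2. Raising 48 by 20% is not the same as allowing for 20% loss, because the loss applies to the number randomised. Multiplying by 1.2 always gives too few.
3. The effect size is given as 0.8, but 13 points on an SD of 16 is 0.8125, and the required number depends on which is used.

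The last two both push the number down. In a small sham-controlled trial a null result is a real possibility, and readers will then look at the stated power. That statement should therefore be correct on its own inputs.

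**Working it through.** **Inputs** (Sample size calculation, Protocol article): difference 21 − 8 = 13 points; SD 16; stated effect size 0.8; alpha 0.05; 0.80, taken as power; 48 evaluable; 58 randomised; about 20% loss. Two-sided alpha is inferred, because a one-sided test gives 19 to 20 per arm and does not reproduce 24.

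**Step 1: reproduce the 48.** Normal approximation, two-sided: n per arm = 2 × (1.96 + 0.8416)² / d².

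- d = 13/16 = 0.8125: n = 23.78, rounded up to 24 per arm, total 48. This matches the article.
- d = 0.8: n = 24.53, rounded up to 25 per arm, total 50.
- A two-sample t-test (noncentral t) needs 25 per arm at 0.8125 and 26 per arm at 0.8.

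The 48 is therefore reproducible, but only from the 13-point difference and the normal approximation.

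**Step 2: beta or power.** With a true beta of 0.80 (power 0.20), the formula gives 2 × (1.96 − 0.8416)² / 0.8125² = 3.8, or 4 per arm. The stated 24 per arm shows that 0.80 was used as power. The label is wrong and the calculation is not.

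**Step 3: the allowance for loss.**

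- 48 × 1.2 = 57.6, rounded up to 58. This matches the article.
- 48 / (1 − 0.20) = 60.
- 58 × 0.80 = 46.4, or about 23 per arm.
- 1 − 48/58 = 17.2%, the largest loss at which 58 still leaves 48.

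**Step 4: nominal power of a simple two-group comparison.** Normal approximation: power = Φ(d × √(n/2) − 1.96). For example, at n = 23 and d = 0.8125: 0.8125 × √11.5 = 2.755; 2.755 − 1.96 = 0.795; Φ(0.795) = 78.7%. The t-test figures use the noncentral t distribution with 2n − 2 degrees of freedom.

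| Evaluable per arm | d | Normal | t-test |
|---|---|---|---|
| 24 (no more than 17.2% lost) | 0.8125 | 80.4% | 78.7% |
| 24 | 0.8 | 79.1% | 77.4% |
| 23 (20% lost) | 0.8125 | 78.7% | 76.9% |
| 23 | 0.8 | 77.4% | 75.6% |

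At the planned 20% loss, none of the four combinations reaches 80%. The gap runs from 1.3 points (80 − 78.7) to 4.4 points (80 − 75.6).

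**The case against.** A reader might infer from the table that the trial fails to deliver its stated power, and that its real power is 76–77%. The documents do not support that, for these reasons.

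- The required 48 is not an error. It follows exactly from 13 points, SD 16 and a standard planning formula, with 80.4% power.
- The article names no test, so holding it to a t-test is the reviewer's choice. Even then, 24 per arm at 13/16 gives 78.7%.
- The 0.8 can be read as a rounding: 0.8 × 16 = 12.8, which rounds to 13.
- Loss is described as approximate, and 17% is arguably within that wording. The shortfall against 60 is two patients.
- The planned analysis is a GEE on all available measurements, not a t-test in those who complete the 4-month visit. Withdrawn patients who are not having other knee OA treatment are invited to complete questionnaires from home (Study population and recruitment). Loss is not tied to the 4-month visit, and follow-up runs to 12 months. Since no within-patient correlation is given, the power of the planned analysis cannot be computed.

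All of this stands, and it limits the point to a small correction. It does not remove it: beta is mislabelled, multiplying by 1.2 is the wrong operation for a 20% loss, and the stated effect size does not give the stated number.

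The opposite inference, that adjusting for baseline KOOS pain would bring power back to 80%, is not supported either. The candidate covariates in the Statistical analysis section are radiographic severity, pressure pain threshold and painDETECT. Baseline KOOS pain is not among them, and no baseline-to-follow-up correlation is given.

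**Conclusion.** Wrong as written, minor severity. The printed beta is the power. The target of 58 protects 48 evaluable patients up to about 17% loss, not 20%. The 24 per arm belongs to 13/16 and not to 0.8.

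After a full 20% loss, nominal power at 13/16 is about 77% to 79%, depending on the formula; at 0.8 it is about 76% to 77%. These figures assume two-sided alpha 0.05, an SD of 16, equal loss in the two arms, and an unadjusted comparison of patients with 4-month data. They check the article's own calculation on its own terms and say nothing about the power of the GEE. A gap of one to four points should not change how a null result is read, which will rest mainly on the confidence interval. The SD of 16 is itself an estimate from other studies.

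**What to change.** Keep 58 and correct the paragraph:

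1. Replace the error rates with: *power 0.80 (beta 0.20), two-sided alpha 0.05*.
2. Use one effect size throughout, 13 points / SD 16 = 0.81, and name the formula (normal approximation for two means).
3. Replace the sentence on loss with one of these:
   - *58 patients allow for about 17% loss while retaining 48*; or
   - *20% loss from 58 leaves 46 evaluable patients, with about 77–79% power for a 13-point difference (SD 16) in an unadjusted two-group comparison*.
4. Add that this figure is for a simple two-group comparison and not for the planned GEE. Make no claim that baseline adjustment restores 80%.

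The cost is text only, with no extra patients and no change to the design or analysis.

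### A lower SD cannot make standardised effects below 0.8 detectable: power at 0.5 is about 40% with 48 evaluable patients and 46% even if all 58 are analysed

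*Protocol article*

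**What the plan says.** All of this is in the Sample size calculation section of the protocol article. The design target is a large effect: "we assumed we would require to demonstrate a large effect size of > 0.8 (strong effect) compared to sham embolization". The inputs are "a standard deviation of 16 for the KOOS (100-0) pain score", "beta of 0.80, and alpha of 0.05", and an improvement of "8 points in the control group (placebo effect) compared to 21 points in the intervention group". The result is that "48 patients (*n* = 24 per study arm) are required". Enrolment is then raised for dropout: "The targeted sample size will be 58 to account for approximately 20% of patients lost to follow-up".

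The section goes on to expect a more homogeneous population because of the entry window on the pain rating (NRS 4 to 8). It concludes that, with this sample size and an SD below 16, "we expect we could also detect smaller effect sizes between 0.5 (moderate effect) and 0.8".

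**The concern.** The section labels 0.5 a moderate effect and 0.8 a strong one, and its 0.8 corresponds to 13 points over an SD of 16. These are standardised effects. Power at a fixed standardised effect depends on the sample size and alpha, not on the SD, so the condition attached to the claim cannot produce the stated gain.

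The trial is a sham-controlled test of efficacy. The Discussion recalls that sham-controlled trials showing no difference led to a procedure being dropped from guidelines. A reader who trusts the sentence could take a non-significant result here as evidence against a moderate benefit of embolization over sham. On the planned numbers, the trial would miss a true effect of 0.5 more often than it would find it.

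**Working it through.** **Inputs** (Sample size calculation section): difference 21 − 8 = 13 points; SD 16; alpha 0.05; power 0.80 (printed as beta); 24 evaluable per arm; 58 enrolled; about 20% loss. Allocation is 1:1 (section on randomization). The sidedness of alpha is not stated.

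**1. Reproducing the plan's figure.** The normal approximation is n per arm = 2(z₀.₉₇₅ + z₀.₈₀)²/d² = 2(1.960 + 0.842)²/d² = 15.70/d².
- d = 13/16 = 0.8125: 15.70/0.660 = 23.8, so 24 per arm and 48 in total. This matches the plan.
- d = 0.8 exactly: 24.5, so 25 per arm.
- One-sided alpha gives 19 to 20 per arm (38 to 40 in total) and does not reproduce 48. Two-sided alpha is used from here on.

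**2. Power at a standardised effect.** Power ≈ Φ(d√(n/2) − 1.96), in which the SD does not appear. For d = 0.5 and n = 24: 0.5 × √12 − 1.96 = −0.23, and Φ(−0.23) = 0.41. The noncentral t gives 0.40, and gives that same value at SD 16, 14, 12, 10 and 8. Other t-based values:

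| Effect size | 23 per arm (58 × 0.8 = 46) | 24 per arm | 29 per arm (no loss) |
|---|---|---|---|
| 0.5 | 0.38 | 0.40 | 0.46 |
| 0.6 | 0.51 | 0.53 | 0.61 |
| 0.7 | 0.64 | 0.66 | 0.75 |
| 0.8 | 0.76 | 0.77 | 0.85 |
| Effect with 80% power | 0.84 | 0.83 | 0.75 |

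With 48 evaluable, no effect from 0.5 to 0.8 reaches 80% power. With all 58 analysed, only effects from about 0.75 upward do.

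**3. Sample size for 0.5.** 15.70/0.25 = 62.8, so 63 per arm (64 by the t-test), or about 126 to 128 evaluable patients.

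**4. What a lower SD does change.** The detectable difference in points is the detectable effect size times the SD.

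| SD | Points detectable with 80% power: 24 / 29 per arm | Power for 8 points: 24 / 29 per arm |
|---|---|---|
| 16 | 13.2 / 12.0 | 0.40 / 0.46 |
| 14 | 11.6 / 10.5 | 0.49 / 0.57 |
| 12 | 9.9 / 9.0 | 0.62 / 0.70 |
| 10 | 8.3 / 7.5 | 0.77 / 0.85 |

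Here 8 points is 0.5 × 16. It reaches 80% power when the SD falls to 8/0.826 = 9.7 (24 per arm) or 8/0.749 = 10.7 (29 per arm). At those SDs the standardised effect is 0.83 or 0.75, not 0.5.

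**The case against.** The strongest defence is that the effect sizes are meant on the planning scale of SD 16, so that the range runs from 8 to 13 points. The condition on the SD then makes sense, and part of the range becomes reachable: at 24 per arm, 11.6 points (0.72 on that scale) at SD 14 and 9.9 points (0.62) at SD 12. This is a fair reading of what may have been intended. It conflicts with calling 0.5 a moderate effect, however, and the lower end still needs an SD near 10.

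Such an SD is not impossible. The 16 is given for the pain score, not explicitly for its change. If it is the SD of the score at each visit, the SD of change is 16√(2(1 − r)), where r is the correlation between visits: 12.4 at an assumed r of 0.7 and 10.1 at 0.8, but 16 again at 0.5. The protocol states no correlation. The entry window it relies on restricts a baseline rating on another scale, and nothing shows how far that narrows the spread of KOOS change.

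The planned analysis, a repeated-measures GEE with possible covariate adjustment, may also be more precise than a t-test at one visit. Assuming a covariate correlated 0.5 to 0.7 with the outcome, power at 0.5 (on the unadjusted SD) rises to 0.50–0.66 at 24 per arm and 0.58–0.75 at 29. Under that assumption the trial would no longer miss the effect more often than not, but power stays below 80%, and the section does not rely on this argument.

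Finally, the sentence is hedged, does not drive the sample size, and sits beside an open statement that a large effect is the target. That limits the harm, but it does not make the claim correct.

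**Conclusion.** The concern holds. The section credits the design with sensitivity it does not have, by a mechanism that cannot work for standardised effects. Power at 0.5 is 0.38 to 0.40 with the 46 to 48 patients expected after dropout, and 0.46 with no loss at all. The effect detectable with 80% power stays at about 0.83 (24 per arm) or 0.75 (29 per arm) at any SD. These figures assume a two-sided 0.05 test and an unadjusted two-group comparison at 4 months, the calculation that reproduces the plan's own 48. The error does not affect the sample size or the primary analysis. It affects how a non-significant result would be read, and should be corrected.

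**What to change.** Replace the sentence with a statement along these lines: with 24 evaluable patients per arm the trial has 80% power for a standardised effect of about 0.83, which is about 13 points at SD 16 or 10 points at SD 12; power for a moderate effect of 0.5 is about 40% (46% if all 58 are analysed), and a non-significant result will not be taken to exclude such an effect. Base any negative conclusion on the confidence interval for the between-group difference in KOOS points.

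If the authors meant 8 to 13 points on the SD-16 scale, they should say so in points and give the evidence for the lower SD of change.

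The cost is text only. Enrolment, conduct and analysis are unchanged; one stated property of the design becomes less favourable.
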